### Therapy drop-out criteria

Patient’s wishMedical condition requiring the discontinuation of therapy in the opinion of the study director or patientInsufficient compliance

In case of early drop-out from the study, the planned follow-up scheme will be continued. For non-evaluable patients, the reason will be recorded in the case report forms. Study patients will have the opportunity to refuse individual investigations.

### Statistical analysis

Due to the explorative character of this study, it was not possible to estimate the total number of cases; with a scheduled number of 30 patients per group, it will, however, be possible to detect a standardized mean-value effect (Cohen’s d) of 0.74 with a power of 80% and a significance level of 5%, if a one-factorial variance analysis is calculated. All variables will be analyzed descriptively by tabulation of the measures of the empirical distributions. In case of continuous variables mean values, standard deviations, median, minimum, and maximum values will be documented. Categorical variables will be documented as occurrence and percentage. The primary endpoint will be measured by CT. Results will be presented at three months after completion of RT and differences between groups will be calculated using a one-factorial variance analysis. Differences of categorical variables will be calculated with the Chi-square test. The survival analysis will be performed using the Kaplan–Meier method and log-rank test.

All statistical analyses will be carried out descriptively using SAS software Version 9.4 or higher (SAS Institute, Cary, NC, USA).

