### Recruitment and randomization

The patients will be given all the relevant information about the study by the radiation oncologist at their first presentation to our department (approximately 1–2 weeks before the start of RT). If patients are interested in participating in the study, they will receive a second appointment in order to further inform them and to obtain informed consent. A block randomization procedure will be used to ensure even distribution of patients into the four groups. The randomization procedure will be carried out by a central office. The study personnel responsible for the recruitment and patient care will have no access to the randomization information and the study director will have no influence on the recruitment of patients. The recruitment phase will be concluded with the attainment of the planned number of patients (120 patients in total, 30 patients in each group). Projected recruitment time will be 12 months, and recruitment is scheduled to start in February 2017. Regular study follow-up will end two years after enrolment or, where applicable, with the respective patient’s death.

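### The detectable effect of d = 0.74 at 80% power matches a two-arm t-test and is not a general property of the four-arm ANOVA to which the protocol attaches it

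*Protocol article*

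**What the plan says.** The Statistical analysis section of the protocol article explains that, because the study is exploratory, the number of cases could not be estimated. It then gives one planning figure. "with a scheduled number of 30 patients per group", the trial can detect a Cohen's d "of 0.74 with a power of 80% and a significance level of 5%, if a one-factorial variance analysis is calculated".

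The same section makes that test the analysis of the 3-month CT result: "differences between groups will be calculated using a one-factorial variance analysis". The Methods/Design section describes four parallel groups, and Recruitment and randomization sets the target at "120 patients in total, 30 patients in each group". The article gives neither a Cohen's f nor a pattern for the four means.

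Therapy drop-out criteria foresees patients without usable data ("For non-evaluable patients, the reason will be recorded in the case report forms") and lets patients decline single investigations. It also keeps the follow-up schedule going after early drop-out.

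**The concern.** Cohen's d is a standardised difference between two means. The omnibus F test over four arms is governed by Cohen's f, the spread of all four means relative to the within-group SD. A single d does not fix f, because the two arms that are not at the extremes also contribute. A power statement for this ANOVA therefore needs either f or a stated pattern of means, and the sentence gives neither.

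This is the only quantitative statement about what 120 patients can show. If it describes a different test from the one named, the reader does not know the sensitivity of the planned primary comparison and cannot tell whether 80% is too high or too low for the pattern of interest.

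**Working it through.** **Inputs from the protocol article.** 30 per group, d = 0.74, 80% power, 5% level and one-factorial ANOVA (Statistical analysis); four arms and 120 patients (Recruitment and randomization). Sidedness is not stated. The t-test below is two-sided; the F test has no sidedness.

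**Step 1: reproduce the stated figure.** Two-sample t-test, n = 30 per arm, df = 58, critical value 2.002, noncentrality δ = d·√(n/2).

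- At d = 0.74, δ = 0.74 × √15 = 2.866, and power is 80.5%.
- Solving for 80% power gives d = 0.736, which rounds to 0.74.

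A single unadjusted contrast that uses the ANOVA error (116 df) is close: 81.1% power at 0.74, detectable d 0.729.

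**Step 2: the four-arm F test.** k = 4, n = 30, df = 3 and 116, critical F = 2.683. The noncentrality is λ = n·Σ(μᵢ − μ̄)²/σ² = 4n·f². Power of 80% needs λ = 11.28, so f = √(11.28/120) = 0.307.

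**Step 3: translate f into the largest difference between arms.** Let d be the largest standardised difference and S = Σ(μᵢ − μ̄)²/(σ²d²). Then λ = n·S·d², and the detectable d is 0.3065/√(S/4).

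| Pattern of the four means | S | λ at d = 0.74 | Power at 0.74 | Detectable d |
|---|---|---|---|---|
| Two extreme, two midway | 0.500 | 8.21 | 65.1% | 0.867 |
| Evenly spaced | 0.556 | 9.13 | 70.2% | 0.823 |
| One arm differs from three | 0.750 | 12.32 | 83.7% | 0.708 |
| Two arms versus two | 1.000 | 16.43 | 93.2% | 0.613 |

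Example for the first row: S = 0.25 + 0 + 0 + 0.25 = 0.5, and λ = 30 × 0.5 × 0.74² = 8.21. None of these four standard patterns returns 0.74 at 80% power.

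**Step 4: fewer evaluable patients (loss rates are assumptions; the article gives none).** Power at d = 0.74:

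| Evaluable per arm | Assumed loss | Two-arm t-test | F, two extreme and two midway | F, two versus two |
|---|---|---|---|---|
| 30 | 0% | 80.5% | 65.1% | 93.2% |
| 27 | 10% | 76.1% | 59.8% | 90.1% |
| 24 | 20% | 70.9% | 54.0% | 85.9% |
| 21 | 30% | 64.8% | 47.8% | 80.2% |

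At 24 per arm, 80% power corresponds to f = 0.344 for the ANOVA and d = 0.83 for one two-arm comparison.

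**The case against.** **The study is exploratory.** The article says so twice, says the number of cases was not estimated, and describes its analyses as descriptive. The 0.74 did not produce the 120. This stands and lowers the severity. It does not make the sentence correct, because the sentence still makes a definite claim for a named test.

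**0.74 lies inside the ANOVA range.** This also stands. Arms at 0, 0, half and the full difference give S = 0.6875, 80.1% power at 0.74 and a detectable d of 0.739. But the article states no such pattern. That a t-test was actually used is an inference from the numerical match; what can be said firmly is that the figure fits a two-arm comparison and that no pattern is given.

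**It may mean one pairwise contrast after the ANOVA.** With pooled error that has 81.1% power, but it is still a two-arm, unadjusted figure. Four arms have six pairs; with Bonferroni over all six, power at 0.74 is 55.6% (58 df) or 57.3% (116 df). The sentence does not say that a single contrast is meant.

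**Stronger readings that the documents do not support.** A reader might infer that the trial is underpowered throughout, or that a corrected figure must be less favourable. The one-arm and two-versus-two patterns contradict both. The article's aim is to compare treatment with and without the boost, and a pure boost effect gives the two-versus-two pattern, where 80% at 0.74 is conservative. A reader might also infer that expected losses make the figure wrong. The sentence is conditional on 30 per group, no loss rate is documented, and follow-up continues after early drop-out. Nor does the article say that a null result will be read as excluding 0.74 SD; a power statement would not license that even if computed correctly.

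**Conclusion.** The point holds as a mislabelled power statement of moderate severity. The 80% power at d = 0.74 fits an unadjusted, two-sided comparison of two arms of 30. For the four-arm ANOVA that the sentence names, the corresponding quantity is f = 0.31. Power at a largest difference of 0.74 SD is 65%, 70%, 84% or 93% for the four standard patterns, so the error has no single direction.

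These results assume normal data with a common SD, equal arms and 30 evaluable patients in each. Evaluability is a secondary caveat only. At an assumed 24 per arm, power at 0.74 SD is 54% for the least favourable pattern and 86% for two arms against two.

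**What to change.** Keep 120 patients and replace the sentence with, for example: *With 30 evaluable patients per arm, the four-group ANOVA has 80% power at the 5% level for f = 0.31 (largest difference between arms 0.61 to 0.87 SD, depending on the pattern of means); a single unadjusted two-arm comparison has 80% power for d = 0.74.*

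Add one line saying that these figures assume a 3-month CT in all 30 patients per arm, with the result for an assumed smaller number. At 24 per arm: f = 0.34 and two-arm d = 0.83; power at 0.74 SD is 54% for two extreme arms with two midway and 86% for two versus two.

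The cost is a sentence or two of text. No patients, arms, endpoints or tests change. Making boost versus no boost the key contrast (60 versus 60, detectable d = 0.52) would be an optional design choice and is not needed to correct this statement.

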### Assessment of the primary and secondary endpoints

The aim of the study is to evaluate local control rates in metastatic bone disease. The primary endpoint is defined by bone remodeling according to density in the metastasis. Bone density will be measured at the irradiated region at baseline and at the three-month time-point after the completion of RT (t_2_). Furthermore, the local control is assessed by CT imaging taken before and at three and six months after radiation treatment. Secondary endpoints are vertebral stability, QoL, fatigue, pain, overall survival, bone survival, pathological fracture, and neurological deficits. The baseline examination will be carried out immediately before the start of therapy and is scheduled to comprise the comprehensive recording of the socio-demographic data, the recording of the current pain situation (VAS score), the extent of fractures, the QoL, and the current degree of fatigue. The follow-up examinations will take place after the end of RT, as mentioned above (Fig. 1).

The secondary endpoints such as overall survival, fatigue, QoL, and anxiety will be recorded by using validated questionnaires (EORTC QLQ FA13 [14], EORTC QLQ BM22 [15], and the questionnaire to record stress in patients with cancer [FBK] according to Book et al. [16]). All patients will also be asked to record their pain history by using a pain diary (documentation of medication daily during treatment and once weekly after the completion of treatment, VAS pain scale). The pain response is documented on the VAS (range of 0–10). Complete response is defined as VAS score of 0/10 after three or six months and partial response is defined as a reduced value by at least 2 points after three or six months, according to the international consensus response categories by Chow et al. [17]. Overall survival is defined as time from initial diagnosis until death and bone survival is defined as time from initial diagnosis of irradiated spinal bone metastasis until death (Additional file 1).

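### The primary one-factor ANOVA leaves baseline bone density out as a covariate and does not say whether 3-month density or change is analysed; ANCOVA would be more precise under either reading

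*Protocol article*

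**What the plan says.** Under Assessment of the primary and secondary endpoints, the protocol article states: "The primary endpoint is defined by bone remodeling according to density in the metastasis". It adds: "Bone density will be measured at the irradiated region at baseline and at the three-month time-point after the completion of RT". A baseline value of the outcome is therefore planned for each patient.

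Under Statistical analysis, the sentence that fixes the primary comparison is: "Results will be presented at three months after completion of RT and differences between groups will be calculated using a one-factorial variance analysis". The precision statement rests on the same model: "with a scheduled number of 30 patients per group", a Cohen's d of 0.74 is said to be detectable with 80% power at the 5% level.

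The article names no covariate, change score or ANCOVA. Under Recruitment and randomization, blocks are used to keep the four arms equal in size, and no balancing on baseline density is described.

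**The concern.** A one-factor analysis of variance has one term, here treatment arm. The Background section describes metastases as osteolytic, osteoplastic or mixed, and the eligibility criteria do not restrict lesion type, so density may already differ considerably between patients before treatment. If the 3-month value is compared alone, whatever part of that spread persists stays in the error term, and a chance baseline difference between arms carries over into the result.

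The dependent variable is also left open. Bone remodelling can be read as a change. A one-factor ANOVA of change would use baseline by subtraction, which is a different analysis with different precision. At stake are the width of the confidence intervals in a trial fixed at 30 per arm, and how an observed difference is to be interpreted if the arms happen to start unequal.

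**Working it through.** **Inputs from the article:** 30 patients per arm, four arms, 80% power, 5% level, d = 0.74. **Assumptions:** two-sided testing; 30 evaluable per arm (no dropout rate is given); equal SD at baseline and 3 months; a common linear slope; and r, the baseline to 3-month correlation, between 0.3 and 0.8. The article gives no value for r.

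**1. The plan's own figure.** A two-sided two-sample t-test with 30 per arm (58 df, noncentral t) detects d = 0.736 with 80% power, and power at 0.74 is 80.5%. The stated 0.74 is thus an unadjusted two-group figure. Using the pooled error of all four arms (116 df), the detectable pairwise difference is 0.7294 SD, the starting point below.

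**2. Variance under the three analyses**, in units of the 3-month variance:
- 3-month value only: 1
- change from baseline: 2(1 − r)
- ANCOVA: 1 − r²

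ANCOVA relative to change is (1 − r²) / [2(1 − r)] = (1 + r)/2. Effective size per arm is 30/(1 − r²) against 3-month-only and 30 × 2/(1 + r) against change. The detectable difference is 0.7294 times the square root of the variance; the one degree of freedom lost to the covariate is negligible.

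| r | 1 − r² | 30 per arm worth, vs 3-month-only | Detectable, ANCOVA (SD) | 2(1 − r) | Detectable, change (SD) | (1 + r)/2 | 30 per arm worth, vs change |
|---|---|---|---|---|---|---|---|
| 0.3 | 0.91 | 33.0 | 0.696 | 1.40 | 0.863 | 0.65 | 46.2 |
| 0.5 | 0.75 | 40.0 | 0.632 | 1.00 | 0.729 | 0.75 | 40.0 |
| 0.7 | 0.51 | 58.8 | 0.521 | 0.60 | 0.565 | 0.85 | 35.3 |
| 0.8 | 0.36 | 83.3 | 0.438 | 0.40 | 0.461 | 0.90 | 33.3 |

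The two readings are equally precise at r = 0.5. Below that, the change score is worse than ignoring baseline. ANCOVA has the lowest variance in every row.

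**3. Chance imbalance.** The baseline difference between two arms of 30 has SD √(2/30) = 0.258 baseline SDs. It exceeds 0.25 SD with probability 33% and 0.5 SD with probability 5%. Across four arms, the range of baseline means exceeds 0.5 SD in 21% of simulated randomisations.

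With no treatment effect and a baseline difference b, the expected 3-month difference is rb and the expected difference in change is (r − 1)b. For b = 0.5 SD:
- r = 0.5: +0.25 SD (3-month-only), −0.25 SD (change)
- r = 0.7: +0.35 SD (3-month-only), −0.15 SD (change)

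The two analyses err in opposite directions; ANCOVA removes the shift. For the 3-month-only pairwise test, the critical difference is about 1.96 × 0.258 = 0.506, and the difference given b has SD 0.258√(1 − r²). The conditional type I error at b = 0.5 is then about 13% (r = 0.5) or 20% (r = 0.7). At b = 0.25 it is 4.7% or 3.6%, so only the larger imbalances inflate it.

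**The case against.** The strongest reply is that the article never says baseline is ignored. The phrase "Results will be presented at three months after completion of RT" fixes the time point, not the dependent variable, and an endpoint called bone remodelling may well be analysed as change. This stands. A reader might infer that the primary analysis makes no use of baseline and that ANCOVA would be worth up to 83 patients per arm. The text does not support that inference: the larger gains at high r hold only if the 3-month value is analysed alone. Under a change-score ANOVA the gain at r = 0.7 or 0.8 is from 30 to about 35 or 33.

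A second reply is that randomisation protects the unadjusted test. This also stands. Over repeated randomisations either ANOVA is unbiased and keeps its 5% type I error. The 13% and 20% above are conditional on an imbalance of 0.5 SD, which two arms reach or exceed about 5% of the time. They do not show an invalid test.

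Third, r is unknown, and at r = 0.3 the gain over a 3-month-only analysis is small (0.73 to 0.70 SD). Correct; for that reason the whole range is shown.

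Fourth, this is a condensed article on an exploratory study, and covariates are often left to an analysis plan. Here, however, the article names the model, says it has one factor, and ties its precision statement to that model. The exploratory label excuses the absence of a confirmatory sample size; it gives no reason to leave a planned baseline measurement out of the model.

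**Conclusion.** The point holds as one of efficiency and clarity. The article commits to a one-factor ANOVA at three months with arm as the only term, plans a baseline density measurement, and does not name the dependent variable. Under either reading the analysis is valid but less precise than ANCOVA, and it handles a chance baseline difference imperfectly.

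For assumed r of 0.3 to 0.8, the gain is equivalent to raising 30 per arm to about 33 to 83 against a 3-month-only analysis, or to about 46 down to 33 against change. These figures rest on equal variances, a common slope and 30 evaluable patients per arm. The last is optimistic, since the article allows patients to refuse individual investigations.

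A reader might go further and conclude that the planned test is biased or its result unusable; randomisation rules that out. Nor does the point extend to pain, quality of life or fatigue, because the article does not state baseline-related models for them that could be judged.

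**What to change.** State 3-month density as the dependent variable. Make the primary analysis an ANCOVA with treatment arm as factor and baseline density of the same irradiated region as covariate. Report adjusted mean differences between arms with 95% confidence intervals, and keep the unadjusted one-factor ANOVA as a sensitivity analysis, saying whether it is run on the 3-month value or on change.

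The cost is a short change to the Statistical analysis section and one error degree of freedom (116 to 115). No extra scan, visit or patient is needed, because the baseline measurement is already planned.

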## Background

Two-thirds of all cancer patients develop bone metastases during the course of their disease [1]. This form of distant relapse occurs from many types of solid cancers, especially from lung, breast, and prostate [2]. Bone involvement can also be extensive in certain hematologic malignancies [3, 4]. About 30% of all skeletal metastases and 10% of all primary bone tumors are located in the spinal column [5], mostly the lumbar (52%), thoracic (36%), and cervical (12%) spine [6]. The exact mechanism of bone metastasis is not fully understood. It is postulated that bone metastases arise as a detachment of tumor cells from the primary tumor and reach the bone by intravascular penetration, resulting in adhesion in distinct bone areas. The tumor cells cause local changes of the bone structure, caused by an imbalance of bone remodeling. Bone metastases present as osteoplastic, osteolytic, or mixed osteolytic/osteoplastic tumor masses. Many metastatic bone lesions cause few or no symptoms, but for skeletal-related events, pain is the most common symptom; many patients with bone metastasis experience significant pain at some point during their disease course [7]. Other skeletal-related events include reduce activity in daily life (ADL), decreased energy, hypercalcemia, and risk of pathological fractures and neurological deficits. Pathologic bone fractures occur in 5% and spinal cord compression in 10–15% [5]. Restrictions of movement of the spinal column may have a devastating long-term impact on function, mobility, independence, health, and quality of life (QoL). External beam radiotherapy has an established role in the management of patients with bone metastases of the spine. The fractionation schedule applying 30 Gray in ten fractions is a safe and effective treatment modality commonly used to achieve palliation of pain associated with spinal metastases [8]. In about 50–80% of the patients, a decrease of pain is reported and about 30% of the patients showed complete remission of pain [8]. Stereotactic body radiation therapy (SBRT) using intensity-modulated radiotherapy (IMRT) can be a safe treatment option for treating spinal metastasis with enhanced targeting accuracy [9, 10]. Published data report that IMRT to the spine was well tolerated, had no significant late toxicities, and spared other organs at risk [11]. Pre-treatment megavoltage computed tomography (CT) allows for the control of the patient position and improves treatment accuracy [12].

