## Methods/Design

This is a prospective, randomized, single-center, controlled, exploratory intervention study with four parallel treatment groups aimed at comparing local control rates after RT with and without SIB in patients with bone metastases of the spine. Four different schedules will be evaluated: IMRT with 30 Gy in ten fractions to the whole vertebral body, IMRT with 30 Gy in ten fractions to the whole vertebral body with the application of a SIB to 40 Gy, 20 Gy in five fractions to the whole vertebral body or IMRT with 20 Gy in five fractions to the whole vertebral body with the application of a SIB to 30 Gy. Before enrolment in the study, patients will receive CT and if necessary magnetic resonance imaging (MRI)-based staging examinations to measure the spinal cord dimension. If intraspinal metastases are suspected, an MRI examination is performed beforehand.

RT is performed in systemic/targeted therapy free interval. Radiation therapy will be applied in five fractions per week (Monday to Friday).

After recording the baseline measurements, patients will be randomly assigned to one of the four groups. Target parameters will be measured and recorded at baseline (t_1_), at week 12 (t_2_), and again at week 24 (t_3_) (Fig. 1). Follow-up measurements are scheduled to take place at 12, 18, and 24 months after the completion of RT (Fig. 2).

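### The three-month density comparison is fixed as a one-factor ANOVA with arm as its only term, although baseline density is already measured and adjusting for it would probably gain precision at almost no cost

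*Protocol article*

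**What the plan says.** All references are to the protocol article.

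- **Endpoint** (Assessment of the primary and secondary endpoints): "The primary endpoint is defined by bone remodeling according to density in the metastasis". The same section adds: "Bone density will be measured at the irradiated region at baseline and at the three-month time-point after the completion of RT". It does not say whether the analysed quantity is the three-month value or the change from baseline.
- **Timing of baseline** (Methods/Design): "After recording the baseline measurements, patients will be randomly assigned to one of the four groups".
- **Analysis** (Statistical analysis): "Results will be presented at three months after completion of RT and differences between groups will be calculated using a one-factorial variance analysis". No covariate is named.
- **Power** (Statistical analysis): the planned size can detect a "standardized mean-value effect (Cohen’s d) of 0.74 with a power of 80% and a significance level of 5"%, on the basis of the same one-factor model.
- **Size** (Recruitment and randomization): "120 patients in total, 30 patients in each group".
- **Lesion types** (Background): "Bone metastases present as osteoplastic, osteolytic, or mixed osteolytic/osteoplastic tumor masses".

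**The concern.** A one-factor ANOVA leaves in the residual all the variation between patients that was present at entry. Here that variation may be large: the cohort can mix bone-forming, bone-destroying and mixed lesions, so density before treatment plausibly differs widely from patient to patient. Baseline density is the natural predictor of three-month density, it is measured before radiotherapy, and the trial already collects it.

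What is at stake is precision. With 30 patients per arm, the trial is sized for a difference of about three quarters of a standard deviation. Smaller density differences between the four schedules could be missed or estimated loosely when data already in hand would sharpen them.

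**Working it through.** **Inputs from the article:** four arms of 30; d = 0.74; power 80%; significance level 5%; one-factor ANOVA.

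**Assumptions:** a two-sided test (the article gives no side); the correlation ρ between baseline and three-month density (not given, so shown as a range); equal variances at the two times for the change-score results.

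**1. Reproducing the stated figure.** For two arms of n, the noncentrality is d·√(n/2) = 0.74·√15 = 2.866.

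- Two-sided t-test with 58 df: power 80.5%; the d for 80% power is 0.736, which rounds to the stated 0.74.
- Same contrast with the four-arm pooled error, 120 − 4 = 116 df: power 81.1%; detectable d 0.729.

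The stated figure is therefore a pairwise contrast. The overall four-group F-test with a largest difference of 0.74 has power from 65.1% to 93.2%, depending on the pattern of means. The base below is the pairwise 81.1%.

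**2. Raw three-month density would have been analysed.** Adding baseline density multiplies the residual variance by (1 − ρ²). Chance imbalance in the covariate adds a factor of about 1 + 1/114 = 1.009, and the error df falls to 115. The effective standardised difference is 0.74/√[(1 − ρ²)·1.009].

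| ρ | 1 − ρ² | effective d | power |
|---|---|---|---|
| arm only | 1.00 | 0.740 | 81.1% |
| 0 | 1.00 | 0.737 | 80.8% |
| 0.3 | 0.91 | 0.772 | 84.3% |
| 0.5 | 0.75 | 0.851 | 90.4% |
| 0.7 | 0.51 | 1.032 | 97.7% |

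Ignoring the small imbalance factor, ρ = 0.5 is worth 30/0.75 = 40 patients per arm.

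**3. Change from baseline would have been analysed.** With equal variances, change has variance 2(1 − ρ) in units of the raw variance, and the adjusted model has 1 − ρ². Their ratio is (1 + ρ)/2, which is never above 1. If d = 0.74 is in SD units of change, the base is again 81.1%, and the effective difference is 0.74/√[((1 + ρ)/2)·1.009].

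| ρ | (1 + ρ)/2 | effective d | power |
|---|---|---|---|
| 0.5 | 0.75 | 0.851 | 90.4% |
| 0.7 | 0.85 | 0.799 | 86.6% |
| 0.8 | 0.90 | 0.777 | 84.7% |

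Here the gain shrinks as ρ rises, because subtracting the baseline already removes most of the shared variation.

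**4. Cost if baseline density predicts nothing.** At ρ = 0, power goes from 81.1% to 80.8%, a loss of about 0.3 percentage point.

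**The case against.** **Condensed article.** The Statistical analysis section is short, and the full protocol or SAP may add covariates. That is fair as far as it goes, and nothing here claims that those documents lack them. But the article does more than leave the model open: it names a one-factor analysis both for the power statement and for the comparison itself. That published choice can be commented on.

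**Change may already be the outcome.** The endpoint is described as bone remodelling, with density taken at two times, so change is a natural reading. This stands, and it limits the size of the gain. A reader might take the raw-value result at ρ = 0.7, worth 30/0.51 = 58.8 patients per arm, as the expected benefit. The article does not support that: the correlation is unknown and the raw-value reading is not established. On the change reading at the same ρ, the equivalent is only 30/0.85 = 35.3 per arm. The direction of the recommendation is the same either way.

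**Exploratory status.** The article calls the study exploratory and its analyses descriptive, so no confirmatory decision rests on one contrast. This also stands and keeps the point modest. It does not remove it, since tighter estimates are useful in a small exploratory trial.

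**Further covariates.** A reader might infer that use of bone-modifying drugs at entry should also be a model term or a randomisation stratum. The article names no such drug and does not show that use is recorded, so relevance, prevalence and effect would all come from outside. Such a term could also add little or nothing once baseline density is in the model, if baseline density already reflects the drug effect. It is not part of this point.

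**Conclusion.** The point holds as a matter of efficiency. The planned ANOVA is valid under randomisation, and a reader who inferred bias or an invalid test would go beyond the documents. It probably leaves precision unused, because a pre-treatment measurement of the outcome is available and not in the model.

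The direction is secure: the adjusted model has residual variance no larger than either unadjusted analysis, apart from a loss of about 0.3 percentage point of power in the worst case. The size is not secure. It rests on a correlation that the article does not give, on whether value or change is analysed, and on which standard deviation the stated 0.74 refers to. Across the ranges shown, power at that effect rises from 81.1% to somewhere between about 84% and 98%.

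These figures also assume all 30 patients per arm are evaluable at three months. The baseline value's standing as a pre-randomisation covariate rests on the order given in Methods/Design. The endpoint section places the baseline examination immediately before therapy starts, which is still before any radiation effect.

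**What to change.** 1. Replace the one-factor ANOVA with a prespecified ANCOVA of three-month density on arm plus baseline density. Using change in density as the outcome gives the same arm contrasts once baseline density is in the model, so this choice also removes the ambiguity between value and change.
2. Use the density measured before allocation, as Methods/Design describes.
3. Keep the unadjusted ANOVA as a supporting analysis, and say whether it is run on the three-month value or on change.

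The cost is one degree of freedom. No additional scan, visit, form field or patient is needed, because baseline density is already measured. The change should be recorded before the outcome data are examined by arm.
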